### The intervention

The intervention will be hosted using LifeGuide and iSurvey platforms, both developed by the University of Southampton. LifeGuide is an open-source software which allows researchers to create online interventions.^36^ iSurvey is a survey generation tool which allows researchers to create and disseminate questionnaires online. Participants will register for the intervention using LifeGuide, which will also host the majority of the questionnaires. iSurvey will be used to host the visual-probe tasks, along with the Engagement with the Online Training questionnaire and the Brief Pain Inventory,^37^ which appear at the end of every visual-probe task session. The flow of sessions is provided in figure 2, and examples of web pages are shown in figure 3. On loading the intervention home page, the individual is provided with a brief welcome to the website and rationale for the intervention. A recent review of cognitive bias meta-analyses concluded that effect sizes were smaller when biases were modified remotely compared with laboratory-based training.^30^ We therefore decided to provide information on the rationale behind ABMT in order to increase motivation and reduce attrition as much as possible, which also mirrors clinical practice that involves educating patients into chronic pain and the psychological interventions used in its management. Individuals are able to either create an iABMT account or log into their existing account. Before any session participants are asked to indicate whether they have enough time and are ready to begin the session. Participants are only permitted to complete one session per day. Should a participant complete their missed session on a subsequently scheduled date (eg, completing their scheduled session from Monday on Thursday instead), all remaining sessions are shifted back accordingly. This process retains the structure of the intervention.

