Our previous lab-based, proof-of-concept ABM intervention found reductions in pain intensity and pain interference from pre-ABM to post-ABM were associated with large effect sizes,^27^ although differences in methodology including delivery (online vs lab-based) and number of sessions warrant a more conservative estimate. On this basis, the study will recruit a minimum of 100 with 1:1:1:1 randomisation. This study is powered primarily to establish treatment efficacy for the primary outcome variable of pain interference by considering baseline and measures after session 10 between those randomised to an attentional modification arm and those randomised to a placebo arm. Randomisation should ensure baseline comparability on measures between these two groups, and a difference in beneficial outcomes between these groups will be modelled using a linear mixed model. For an assumed correlation of 0.7 between baseline and end of session 10 measures, a total of 40 per group (ie, 20 per randomised arm) would be needed to detect small to moderate standardised intervention differences (Cohen’s *d*=0.25) with at least 80% power (alpha=0.05, two-sided). The recruitment strategy includes a 20% oversampling to mitigate a loss of power from loss to follow-up.

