### Procedure

Interested individuals will contact the researchers on the details provided in study advertisements and will be assessed against the inclusion and exclusion criteria via telephone interview. If eligible, they will receive a copy of the participant information sheet detailing the requirements and procedure of the study, along with a link to the study website which provides further details on ABM and the research team. If the individual consents to take part, they will be required to create an online ABM account. During registration, participants will select their preferred days for training, which will be either (1) Monday/Thursday or (2) Tuesday/Friday.

Session 1 is the baseline session, and includes the first assessment visual-probe task measuring attentional biases prior to beginning the intervention, along with the questionnaire battery assessing the primary and secondary outcome measures. Randomisation will take place following session 1, where participants will be informed of the length of their training (ie, 4 or 8 weeks). Participants randomised to either of the 10-session conditions will complete four pictorial and four linguistic training sessions, while those randomised to either of the 18-session conditions will complete eight pictorial and eight linguistic training sessions (baseline and endline assessment sessions comprise the remainder of the 10/18 sessions). Participants’ attentional biases will be reassessed at endline (ie, during the final session 10/18) using the same assessment version of the visual-probe task (ie, featuring the same stimuli) used at baseline and the same questionnaire battery. Participants randomised to either of the 18-session conditions will also have their attentional biases reassessed in session 10 after their training session.

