### Analyses of the RCT data

#### Quantitative analyses

A full and detailed statistical analysis plan will be written prior to trial closure. In brief, the data analysis will be performed on an intention-to-treat (ITT) basis to provide an unbiased estimate of the treatment effect.^56^ Per-protocol analyses will also be performed (comprising those correctly randomised, without protocol violations, and providing complete data on the primary outcome measure). Sweetman and Doig^57^ have identified five types of protocol violations, namely violations in (1) enrolment (ie, failure to correctly apply eligibility criteria resulting in the enrolment of an inappropriate participant); (2) randomisation (ie, violation of intended randomisation sequence); (3) study intervention (ie, dosing, timing or delivery errors attributable to members of the research team); (4) patient compliance (ie, participants failing to comply with the trial protocol or other requirements of participation in the trial, such as skipping scheduled appointments or sessions); and (5) data collection (ie, a failure by the research team to comply with prespecific trial guidelines for data collection and/or outcome evaluation due to avoidable reasons). Any such violations will be clearly reported.

Analyses undertaken will include the following:

The primary analysis on pain interference will use the initial 2×2×2 structure comprising stage (baseline, 10 weeks), randomised treatment (attentional bias modification training (ABMT), placebo) and randomised number of sessions (10, 18). This comparison will be extended to compare 10AMG and 10PTG after 10 sessions, and to compare 18AMG and 18PTG after 10 sessions.An analysis of pain interference will use the 2×2×3 structure comprising randomised treatment (ABMT, placebo), randomised number of sessions (10, 18) and stage (baseline, endline, follow-up).An assessment of change in pain interference, both within and between groups, for 18AMG and 18PTG, between the end of session 10 and endline.The four randomised arms compared against one another on pain interference at each of baseline, after session 10, endline and follow-up.An age (16–24, 25–60) subgroup analysis using an age subgroup by treatment effect interaction. These analyses will be an extension of (1), (2) and (3) to incorporate age as a subgroup factor.

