### Ethics and dissemination

The study protocol was registered with ClinicalTrials.gov, with a planned start date of September 2020 and a planned end date of September 2022. All data will remain confidential and stored on password-protected systems and databases. LifeGuide and iSurvey servers both use HTTPS (hypertext transfer protocol secure) connections for security purposes. All data will be anonymised prior to dissemination, and personally identifiable information not known to anyone other than the researchers. Participants may withdraw from the intervention at any point by contacting the researchers via email or telephone, or by simply opting not to log into their iABMT account for their scheduled sessions. Participants are also encouraged to contact the researchers should they experience any distress or discomfort completing the intervention. As per university policy, any adverse events, harms or complaints arising from participation in the intervention will be reported to the University of Southampton Research Governance Office. Findings will be published in the most relevant, high-impact, peer-reviewed journals and presented at relevant conferences. Lay reports will be written for interested pain charities and patient support groups.

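### Session-10 and endline outcomes follow training progress with no stated collection after training stops, so missing primary data will track non-adherence and the unbiased ITT claim rests on MAR

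*Protocol article*

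**What the plan says.** All references are to the protocol article.

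- **Primary time point.** Randomisation and sample size powers the trial on pain interference at baseline and after session 10, comparing the attentional modification arms with the placebo arms.
- **Endline.** Under Procedure, attentional biases "will be reassessed at endline (ie, during the final session 10/18"), together with the same questionnaire battery. Outcome measures adds that the 18-session arms also complete the questionnaires after session 10.
- **Follow-up.** Procedure counts the 6-month invitation from the last session.
- **Missed sessions.** Under The intervention, if a participant makes up a missed session on a later scheduled date, "all remaining sessions are shifted back accordingly".
- **Leaving.** Ethics and dissemination lets participants withdraw from the intervention by contacting the researchers or "by simply opting not to log into their iABMT account for their scheduled sessions".
- **Where the primary instrument sits.** The intervention places the Brief Pain Inventory at the end of every visual-probe session. Table 1 lists the BPI-SF only at baseline, evaluation and follow-up.
- **Analysis.** Quantitative analyses states that "the data analysis will be performed on an intention-to-treat (ITT) basis to provide an unbiased estimate of the treatment effect". The primary model has two stages, baseline and the post-session-10 measure. A mixed model on all available data is said to adhere to ITT. Multiple imputation is secondary, and a sensitivity analysis shifts imputed values by group-dependent amounts to represent departures from MAR.

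**The concern.** Each assessment after baseline is reached by moving through the training sequence, and no other route to the session-10 or endline outcome is described. Someone who stops at session 6 does not arrive at session 10, and the article does not say that the questionnaires will be sought from that person anyway. If the trial is run as written, stopping training and missing the primary outcome will largely coincide.

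Two consequences follow. First, missingness is driven by adherence, which is where MAR is hardest to defend. A participant with only a baseline value adds little or nothing on change in a two-stage model, so the treatment estimate is carried by those who reached session 10. It is also less distinct from the planned per-protocol estimate than it appears, because that set requires complete primary data and no compliance violations. Second, a slow participant is measured later after randomisation than a prompt one, so the calendar time of the primary measure varies with adherence.

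No later analysis plan can recover outcomes that were never collected, so this has to be settled before recruitment.

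**Working it through.** **1. The plan's own figures.** Inputs, all from Randomisation and sample size: d=0.25; "For an assumed correlation of 0.7 between baseline and end of session 10 measures"; "a total of 40 per group (ie, 20 per randomised arm"); "with at least 80% power (alpha=0.05, two-sided"); at least 100 recruited, with a 20% allowance for loss.

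The 40 per group reproduces with a two-group, two-time repeated-measures interaction F test. Effect f = d/2 = 0.125 and noncentrality λ = f² × N × 2/(1 − ρ).

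- At N=80: λ = 0.015625 × 160/0.3 = 8.33, power 0.814. The smallest N reaching 80% is 78.
- Recruitment: 80/(1 − 0.20) = 100.

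So the 20% allowance leaves exactly the 80 evaluable participants the calculation needs. (Whether this convention suits the stated d is a separate question. It corresponds to a 0.5 SD difference in change.)

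**2. Effect in all randomised participants against the completer-driven estimate.** Let q be the proportion without a session-10 measure because they stopped. Assumptions: q is equal in the two treatment groups; there is no treatment difference among those who stop; the difference among completers is the plan's d=0.25. The effect in all randomised participants is (1 − q) × 0.25 + q × 0. A MAR analysis with only baseline data on stoppers points to about 0.25. Only q=20% comes from the plan, and there it is a general loss allowance rather than a forecast of stopping. The other rates are assumed.

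| q | Effect, all randomised (SD) | Completer-driven (SD) | Ratio |
|---|---|---|---|
| 20% | 0.80 × 0.25 = 0.20 | 0.25 | 1.25 |
| 30% | 0.70 × 0.25 = 0.175 | 0.25 | 1.43 |
| 40% | 0.60 × 0.25 = 0.15 | 0.25 | 1.67 |
| 50% | 0.50 × 0.25 = 0.125 | 0.25 | 2.00 |

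The ratio is 1/(1 − q) and does not depend on the effect size chosen. If stoppers keep part of the benefit, the gap shrinks in proportion.

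**3. Precision if loss exceeds the allowance.** With the formula of step 1 and f held at 0.125, 80, 70, 60 and 50 evaluable participants out of 100 give power of 0.81, 0.76, 0.69 and 0.61.

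The remedy should not be presented as a gain in power. Under the zero-benefit assumption, measuring all 100 at q=20% scales f to 0.8 × 0.125 = 0.10, so λ = 0.01 × 200/0.3 = 6.67, below 8.33. The gain is an estimate that answers the ITT question.

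**4. The passages on the BPI.** Read literally, The intervention would give someone who stops after session 6 several earlier BPI scores. Table 1 gives none between baseline and evaluation. The two conflict. Even on the first reading, interim scores are not part of the two-stage primary model. They could serve as auxiliary variables in the imputation, but the article does not say that they will.

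**The case against.** A reader might infer more than this: that outcomes can be obtained only by completing sessions, that those who stop are lost by design, and that the ITT claim therefore cannot hold. The documents do not support that.

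- Nothing bars a person who has stopped training from the questionnaires. The article is condensed, and the session-flow figure and supplements are not shown.
- The withdrawal sentence concerns leaving the intervention. It does not say that follow-up ends, and it is compatible with continued assessment.
- The shift rule covers sessions made up late. Those participants still reach session 10, so the rule shows drift in timing and says nothing about people who stop.
- The last session could mean the last one completed, in which case the 6-month invitation still reaches stoppers.
- Participants can be analysed as randomised with outcomes missing. The planned imputation with group-dependent shifts is a proper test of departures from MAR, and a grid of shifts needs no off-training data to be run.
- Measuring after session 10 is a deliberate choice. Replacing it wholly with a calendar date would change the question from outcome after a set number of sessions to outcome at a set time.

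All of this stands, and it limits the point. It does not remove it. The article positively fixes session-based anchors and an unqualified claim of an unbiased estimate, and it gives no route to the session-10 outcome after stopping. A wider reading of the last session helps at 6 months but not at the primary time point. The shift analysis can show how far conclusions bend, but no observed off-training outcomes would show which shifts are plausible.

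**Conclusion.** The point holds in limited form. As described, collection of the session-10 and endline outcomes follows progress through training, so missing primary data will track non-adherence. The ITT estimate is then unbiased only under MAR, and the article should say so. It does not follow that ITT is impossible or that data on stoppers are certain to be lost.

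On the stated assumptions (no treatment difference in stoppers, equal loss by arm, 0.25 SD in completers), the completer-driven figure exceeds the effect in all randomised participants by 0.05 SD at the plan's 20% allowance, and by 0.075 to 0.125 SD at assumed losses of 30 to 50%. These are illustrations: the article gives no expected rate of stopping and no information on outcomes after stopping. The conflict between The intervention and Table 1 over when the BPI is given is a separate, plain inconsistency. This is a worthwhile, inexpensive improvement rather than a fatal flaw.

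**What to change.** - Keep the session-10 and final-session assessments for those who reach them. For anyone who has not done so by a stated window after the due date, counted from randomisation, send the online questionnaires (at least the BPI-SF) regardless of sessions completed.
- State that due date in calendar terms. The article labels the primary stage as 10 weeks in Quantitative analyses but describes ten sessions over four weeks, given twice a week, in Randomisation and sample size. These need reconciling first.
- Define the 6-month anchor for those who never reach the final session.
- State that not logging in means stopping training, and that follow-up ends only on explicit withdrawal from the study.
- Include these responses in the ITT analysis, and qualify unbiased as conditional on MAR.
- Reconcile The intervention with Table 1 on when the BPI is collected. If it is collected every session, say how the interim scores will be used.

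**Cost.** Some platform set-up, since the BPI currently sits with the task sessions in iSurvey; a few more contacts with people who have stopped training; and some primary measures taken after fewer than 10 sessions, which should be reported as such. No participant's training changes.

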**Figure 2 F2:**
[figure not shown]
Flow of the visual-probe task sessions for the 10-week and 18-week groups in the study. AMG, attentional modification group; PTG, placebo training group.

**Figure 3 F3:**
[figure not shown]
Examples of LifeGuide web pages included in the internet-delivered attentional bias modification training intervention.

Guidance has been informed by research showing attention to be a limited capacity resource,^38 39^ sleepiness to negatively influence concentration and performance,^40^ alcohol to impair speed of information processing and cognition,^41^ energy drinks to be associated with restlessness and nervousness,^42^ caffeine to improve alertness,^43^ large meals to be associated with impairments in cognitive functioning,^44^ and hunger to influence patterns of attention.^45 46^ Participants are provided with guidance to ensure concentration and comfort are maintained throughout each session: (1) allowing enough time for the session with no anticipated distractions; (2) adjusting screen brightness to match the brightness of the environment; (3) closing distracting applications such as Twitter and Facebook; (4) avoiding completing the session when tired; (5) not consuming alcohol at least 3 hours prior to the session; (6) caution in the use of energy drinks which may cause restlessness; (7) if the participant is a coffee or tea drinker, suggesting a cup 30 min prior to the session; and (8) avoiding completing the session when hungry or directly after a meal.

### Visual-probe tasks

The flow of visual-probe sessions is illustrated in figure 2. In total there will be eight linguistic and eight pictorial probe-classification visual-probe training tasks used in the study, each with different stimuli. A complete description of the stimuli including ratings of valence, arousal, pain intensity, written frequency and low-level features is provided in online supplementary material 1. To briefly summarise, each linguistic visual-probe task includes 32 threatening/neutral and 16 neutral/neutral word pairs. Each task includes eight threatening words from each of the following categories: sensory pain, affective pain, health threat and general threat. Each pictorial task includes 32 threatening/neutral and 16 neutral/neutral image pairs. Each task includes eight threatening images from the following categories: musculoskeletal pain, facial expressions of pain, health threat and general threat. A total of 384 trials are included in each task, with each stimuli pair presented four times for 500 ms and four times for 1250 ms. Within each exposure duration, each stimulus appears twice in the upper location of the screen and twice in the lower location.

10.1136/bmjopen-2019-030607.supp1Supplementary data

A separate linguistic visual-probe task will be used in the three assessment sessions, featuring different stimuli to the linguistic training visual-probe tasks. The use of separate assessment and training stimuli is necessary to establish whether training effects generalise to novel stimuli not used in the actual training. The same assessment stimuli will be used in all assessment sessions. The ABM training version of the visual-probe task to be completed by AMG groups includes three main stages per trial (figure 1). Following a 500 ms initial fixation point, a stimulus pair is presented in distinct locations (eg, above and below the initial fixation point) for either 500 or 1250 ms. The stimulus pair may be either words or images, although critically includes one threat-related and one neutral stimulus. Stimuli presentation times of 500 and 1250 ms are used as these are the most common stimuli presentation times adopted in chronic pain visual-probe studies (eg, refs 18 20 47) and will allow us to closely compare our results with those of previous research. Immediately following their presentation, the stimuli disappear and a probe appears (either *‘p’* or *‘q’*) in the location of the neutral stimulus. Participants use corresponding keys on their keyboard to indicate the probe letter as quickly and as accurately as possible. In the standard version of this paradigm completed by PTG groups and used in the assessment sessions, the probe replaces the neutral and threat-related stimulus an equal number of times. The probe-classification version of the visual-prove task is argued to encourage a more even monitoring of the display than the probe-position version (ie, which requires participants to indicate the location of a dot, either left/right or up/down), as for the latter participants can adopt biased monitoring strategies favouring one particular region over the other.^48^ As any such biases in monitoring may affect training, we will use the probe-classification version of the visual-probe task.

### Outcome measures

The primary outcome measure of pain interference will be assessed by the Brief Pain Inventory-Short Form.^37^ Pain interference will be scored as the mean of seven interference items (ie, general activity, walking, work, mood, enjoyment of life, relations with others and sleep). Following guidance in the Brief Pain Inventory User Guide^49^ and also Initiative on Methods, Measurement, and Pain Assessment in Clinical Trials (IMMPACT) recommendations for assessing pain in clinical trials,^50^ we will include individual assessments of ‘worst’, ‘least’, ‘average’ and ‘now’ (ie, current) pain intensity as secondary outcome measures. Additional secondary outcome measures of state and trait anxiety will be assessed by the State Trait Anxiety Inventory,^51^ depression by the Hospital Anxiety and Depression Scale,^52^ pain-related fear by the Fear of Pain Questionnaire III,^53^ sleeping impairment by the Medical Outcomes Study-Sleep Scale,^54^ and engagement to and satisfaction with the online visual-probe training task by the Satisfaction with the Online Training questionnaire (SOT)^55^ and the Engagement with the Online Training questionnaire (EOT). A demographic questionnaire developed by the researchers will be used at baseline to collect information on participants’ age, gender, ethnicity, socioeconomic status, place of residence and pain characteristics. Aside from the SOT and EOT, questionnaires in the 10-session groups (10AMG and 10PTG) will be administered to participants at baseline, after 10 sessions and at 6-month follow-up. In the 18-session groups (18AMG and 18PTG), questionnaires will be administered to participants at baseline, after 10 sessions, after 18 sessions and at 6-month follow-up. At endline for each participant, we will also assess whether the participant and researchers became aware at any point prior to endline which group they had been allocated to. Full details on each outcome measure are provided in online supplementary material 2.

10.1136/bmjopen-2019-030607.supp2Supplementary data

